### Study aims and hypotheses

The goal of the POKAL-PSY study is to find relevant risk-factors and predictors determining the severity of unipolar depression in an outpatient setting with a data driven approach. In Addition, easily retrievable parameters should be used to facilitate the diagnostic process in an outpatient setting. To achieve this, we will use clinical parameters as well as a wide array of biological markers such as IGF-1, cortisol, AAT-1, and HRV measurements. We will recruit three cohorts consisting of outpatients with depression at inclusion, patients in primary care without psychiatric disorders, as well as healthy controls with no prior medical history. Moreover, in a cross-sectional analysis, we are aiming to determine whether we can use data-driven algorithms to identify new relevant sub-categories of unipolar depression that are not yet included in current classification systems. In a further step we would investigate the outcomes of each subcategory.

Accordingly, we assume:Functional and structural physiological correlates exist (autonomic nervous system, blood count, inflammatory parameters, fat distribution patterns) that are altered in the presence of depression compared to healthy, or somatically ill but not depressed patients.Physiological and phenotypic differences exist within the overall population of all depressed patients, which influence the outcome and further course of the disease.

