## Methods and design

The POKAL-PSY study is a prospective study with three cohorts, where we recruit one cohort with healthy controls (*n* = 50), patients with depression (*n* = 475) and participants without depression (*n* = 425) where participants are monitored for five years. Notably, our emphasis on recruiting individuals with and without depressive symptoms serves to comprehensively investigate the predictors and underlying mechanisms of unipolar depression. The inclusion of patients with somatic comorbidities, who frequently seek medical care, highlights a real-world scenario. For this project, participants will be recruited in a naturalistic setting. Cardiovascular factors (heart rate variability, pulse, blood pressure), metabolic factors (blood lipids, HbA1c, body fat percentage, fasting glucose, IGF-1), as well as inflammatory markers (CRP, AAT-1) will be collected. In addition, the burden of somatic symptoms, lifestyle factors (Eating behavior, chronotype, physical activity), psychopathological characteristics (depression subtype, childhood trauma, anxiety) will be assessed by questionnaires. Depressive relapses will be assessed anamnestically if they occur during the follow-up visits. Patients will be mainly recruited in general practitioner (GP) offices, affiliated with the Bavarian Research Practice Network. Currently, we are recruiting at three different sites. By the end of the recruiting process, our goal is to have recruited from 5 to 6 different sites. We plan to recruit 90% of our study cohort within several GP offices. The inclusion and exclusion criteria are checked in consultation with the treating GPs and in direct patient contact by the study staff and the patients' written consent is obtained. In addition, participants will be recruited at the psychiatric outpatient clinic of the university clinic in Munich. In the context of the POKAL project we cooperate with other research groups and projects by providing validation datasets and support concerning participant recruitment. Specifically, we will cooperate with the MIP3 project (project nr. 21–0357, German Clinical Trials Register number: DRKS00025946). The healthy controls recruited will consist of motivated German citizens. All study personnel were trained to conduct the HRV measurements, as well as the observer ratings. Organizational project management is performed by the Studienzentrum Psychiatrie (SZP) of the LMU Munich. All participants sign a written informed consent form prior to participation. The study was approved by the local ethics committee (project nr. 22–0637, date 14.09.2022) and registered at ClinicalTrials.gov (NCT05547711) and at the German Clinical Trials Register (DRKS00030203). The study presented here is a subproject of the research network POKAL (Predictors and Clinical Outcomes in Depressive Disorders; GRK 2621), which is sponsored by the German Research Foundation (DFG) [70]. Furthermore, all the participants are kindly asked whether they give written consent to participate in the Munich Mental Health Biobank, as well [71]. The POKAL-PSY study is performed in accordance with the regulations of good clinical practice and the declaration of Helsinki [72]. The eligibility criteria can be seen in Table 1.

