### Planned data analyses

Categorical data will be one-hot-encoded if suitable and summarized with percentages and confidence intervals. For ordinal data the median will be given as well as the interquartile range and for continuous data we calculate the mean as well as the standard deviation and the confidence intervals. Demographic and baseline characteristics in the study arms will be compared with suitable statistical tests. Since multiple comparisons will be performed significant *p*.values will be reported false discovery rate corrected [107]. With the cross-sectional data at inclusion a SEM analysis will be conducted [108]. Furthermore, we will investigate the predictive value of baseline biological parameters for change in depressive symptomatology. In addition, we will design a classification algorithm using all relevant data detecting which participant is depressed. This approach involves the implementation of multiple supervised machine learning algorithms to thoroughly assess their performance. We will evaluate each algorithm during the analysis stage and subsequently select the one that yields the most favorable results. These algorithms may include, but are not limited to, support vector machines, decision trees, and neural networks. Each of these algorithms will be carefully applied and evaluated in the context of our research question. Furthermore, we will use multimodal stacked algorithms to assess the generalizability of different clinical questionnaires and biomarkers separately. To ensure the robustness of our algorithm selection and model performance assessment, we will employ a leave-site-out nested cross-validation approach in each model. This mitigates the risk of overfitting and ensures generalizability. Since the eventual goal of our algorithm is the implementation in a clinical context and to guide general practitioners, we plan to develop a sequential prediction model, which reduces the number of required data modalities and diagnostic uncertainty, as described by Koutsouleris et al. [109]. Sequential stacking models can be used to reduce the data required to produce optimum prediction scores. This method can greatly increase clinical applicability since physicians will be only asked for additional information if needed to achieve satisfactory predictive accuracy [109].

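### Choosing between algorithms appears to sit outside the nested cross-validation, so the winner's performance would be mildly optimistic and cannot back a guarantee of generalizability

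*Protocol article*

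**What the plan says.** All main statements are in the protocol article, section Planned data analyses, where the classifier that separates depressed from non-depressed participants is described.

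- Selection rule: "We will evaluate each algorithm during the analysis stage and subsequently select the one that yields the most favorable results".
- Candidates: "These algorithms may include, but are not limited to, support vector machines, decision trees, and neural networks". Stacked and sequential models are added later in the same section.
- Validation: "To ensure the robustness of our algorithm selection and model performance assessment, we will employ a leave-site-out nested cross-validation approach in each model".
- What is claimed for it: "This mitigates the risk of overfitting and ensures generalizability".

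Other sections bear on the point. Secondary outcomes foresees a test of the cross-sectional algorithm on follow-up data, which come from the same participants. The Discussion (Development of an algorithm to detect unipolar depression) leaves validation to a later study. On sites, Methods and design says "Currently, we are recruiting at three different sites" and gives a goal of 5 to 6, with 90% of the cohort from GP offices. The same section adds that "participants will be recruited at the psychiatric outpatient clinic of the university clinic in Munich". Study aims and hypotheses describes the non-depressed patient cohort as "patients in primary care without psychiatric disorders". The 50 healthy controls are not assigned to a site.

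**The concern.** Nested cross-validation gives an honest performance figure only for choices made in the inner loop. If each algorithm has its own nested run, its tuning is protected, but each run delivers one outer-fold result per algorithm. Comparing those results and keeping the best is a further choice, made on the very data meant to judge the winner. The figure then reported is a maximum over candidates. Its expectation exceeds the winner's true performance whenever the candidates are close, and the excess grows with the number tried, which the article leaves open.

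Table 1 gives the study goal as a machine learning algorithm that facilitates the diagnosis of depression, so this figure is a main product of the study. Nothing else described would correct it: the follow-up data are not an independent sample, and external validation lies outside this study.

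**Working it through.** The article states no performance figure, so there is none to reproduce. The check asks how large the optimism would be if the choice is made on outer-fold results.

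**Inputs from the article.** 475 participants with and 475 without depression (Power calculation); at least three algorithm types, list open (Planned data analyses); 5 to 6 sites and 90% from GP offices, so 0.90 × 950 = 855 from GP offices and 95 from elsewhere (Methods and design).

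**Assumptions.** K equally good algorithms; true AUC 0.70, with 0.65 as a variant; correlation r between the algorithms' AUC estimates from 0 to 0.8.

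**Step 1. Standard error of one pooled AUC (Hanley-McNeil).** With Q1 = A/(2−A) and Q2 = 2A²/(1+A),

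SE² = [A(1−A) + (n1−1)(Q1−A²) + (n0−1)(Q2−A²)]/(n1·n0).

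For A = 0.70: Q1 = 0.5385 and Q2 = 0.5765, so SE² = [0.21 + 474 × 0.0485 + 474 × 0.0865]/225,625, and SE = 0.0169. For A = 0.65, SE = 0.0177.

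**Step 2. Optimism = E[max of K standard normals with correlation r] × SE**, here with SE 0.0169:

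| K | r = 0.8 | r = 0.5 | r = 0 |
|---|---|---|---|
| 3 | 0.381 × SE = 0.006 | 0.602 × SE = 0.010 | 0.846 × SE = 0.014 |
| 5 | 0.521 × SE = 0.009 | 0.823 × SE = 0.014 | 1.162 × SE = 0.020 |

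With SE 0.0177 (AUC 0.65) the ranges are 0.007 to 0.015 for K = 3 and 0.009 to 0.021 for K = 5. A separate simulation of correlated scores (AUC 0.65, score correlation 0.6, n = 870) gave 0.014 for the best of five, inside that range.

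**Step 3. A less favourable metric.** Suppose the choice uses the plain mean of five site AUCs (855/5 = 171 per site, SE 0.0399 each) and each algorithm's AUC varies between sites with an assumed SD of 0.05. The SE becomes √[(0.0399² + 0.05²)/5] = 0.0286. The optimism is then 0.011 to 0.024 for K = 3 and 0.015 to 0.033 for K = 5.

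**Step 4. Candidates that really differ.** A leave-site-out simulation with five GP sites of 171, a clinic of 95 and five linear candidates of unequal accuracy gave a mean optimism of 0.001 (SE 0.001). It compared models trained without one site with a refit on all sites, so it includes a small offsetting effect of the smaller training set.

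**Step 5. What 5 to 6 sites can show.** With the same assumed between-site SD of 0.05, the 95% half-width of the mean AUC is t(0.975, k−1) × 0.05/√k: 0.062 for k = 5 and 0.052 for k = 6. This is imprecision, not selection bias, but it bears on how much generalizability can be claimed.

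**Step 6. The clinic, conditionally.** Of the 95 non-GP participants, 95 − 50 = 45 would remain for the clinic if all healthy controls are among the 95. A fold with only depressed participants has no AUC or specificity. At sensitivity 0.80 the 95% half-width is 1.96 × √(0.80 × 0.20/n), about 0.12 for n = 45 and 0.08 for n = 95. When the clinic in the step 4 simulation was made single-class, the optimism was −0.001 (SE 0.001): one fold's AUC was lost and no upward bias was added.

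**The case against.** The strongest reply is that the validation sentence names algorithm selection as one of the things the nesting serves, which fits selection in the inner loop. This has weight. The article never says whether the choice uses inner or outer results, or which figure is reported for the winner, so selection on the reported results is not an established fact. But the order given is evaluation first and selection afterwards, and the nesting is applied model by model. Inner-loop selection would be one procedure across all candidates. The wording leans towards outer-fold selection and at best leaves the matter open.

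A second reply is that the article is more cautious elsewhere: it says only that overfitting is mitigated, and the Discussion calls for a validation study. That is fair, and a reader who infers a claim of an unbiased estimate goes beyond the text. The unqualified assurance of generalizability remains.

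A third is that the effect is small. That stands. Larger values would need a choice made on a single site or among some twenty candidates, and the article describes neither.

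A reader might also infer that the psychiatric clinic is a fold of depressed participants only and inflates the accuracy. The article gives no case mix, number or fold assignment for the clinic, and if the healthy controls are seen there the fold has both classes. A single-class fold would also still vary in severity, so the primary outcome, which predicts severity, could be evaluated in it.

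**Conclusion.** The point holds in a limited form. On its natural reading, the plan chooses between algorithms on outer-fold results and describes no untouched data for judging the winner. The winner's performance is then optimistic, and the scheme does not ensure generalizability.

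For three to five similar algorithms at full sample the excess is roughly 0.01 to 0.02 AUC. It could reach about 0.03 under the harsher assumptions of step 3 and is near zero when one algorithm clearly wins. These figures rest on the assumed AUC, correlations, number of candidates and between-site SD. They apply to the depressed/not-depressed classifier; the size for severity prediction was not calculated.

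The clinic fold is a secondary and conditional matter. It would leave two measures undefined in one fold and has no shown upward effect.

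**What to change.** 1. State that the choice of algorithm and of stacking scheme is treated as a hyperparameter and made in the inner leave-site-out loop, from a candidate list fixed before any outer fold is evaluated.
2. Report the outer-fold performance of that whole selection procedure, with the value for each site.
3. Replace the assurance of generalizability by a statement that fits 5 to 6 sites and points to the later validation study.
4. State whether the clinic forms its own fold and where the healthy controls belong. If the clinic fold contains only depressed participants, report sensitivity alone for it. Keeping clinic participants in training only would not help, because it would preserve the link between site and label.

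The cost is wording, computing time and a slightly lower stated accuracy. Recruitment is expected to end in October 2027 (Study progress), so the text can be settled before the final analysis.

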## Study progress

Recruitment for the POKAL-PSY Study began on October 25, 2022. As of September 1, 2023, a total of 230 participants have been enrolled. The recruitment of new patients is anticipated to conclude by October 15, 2027. The current protocol version is 3.0, last revised on July 25, 2023.

Figure 2: This figure outlines the strategic plan for the POKAL-PSY project, detailing key phases and milestones

**Fig. 2 Fig2:**
[figure not shown]
POKAL-PSY study timeline

## Dissemination

The results of the trial will be analyzed and published after analysis. The results will be reported in the first instance to the study collaborators and the DFG. A summary of the study findings will be made available on the POKAL website (www.pokal-kolleg.de). Scientific publication of the results will be attempted in peer reviewed journals. Further, a dissemination concerning research results will be enabled by the POKAL network and associated programs.

## Discussion

The search for biomarkers to diagnose depression is an endeavor being pursued in psychiatric research since the 1980s [111], but barely resulted in application in clinical practice. The successful application remains challenging since the symptomatology of depression is very heterogeneous and on the other hand because there is no diagnostic gold standard that focuses on an underlying biological mechanism [112]. Despite knowing about the metabolic, endocrine, inflammatory as well as autonomous dysregulation that has been observed in depressed patients, none of these are broadly used to stratify patients. For example, cortisol is a well-studied blood biomarker that has been found to predict an onset or relapse of unipolar depression [113]. Nevertheless, measuring cortisol barely plays a role in clinical practice. One possible reason is that changes in the HPA axis are not specifically found in unipolar depression [114]. Further, many studies found contradicting results which might be due to the heterogeneous nature of the disorder [38]. Patients with the diagnosis of “unipolar depression” are phenotypically, genetically and biologically differing, eventually impacting any biological approaches to better understand depression [115]. Furthermore, exploring potential biomarkers mostly cross-sectional studies were performed which are inherently unable to distinguish consequences secondarily to the illness from alterations caused by the disease itself [116]. Prospective evidence is dearly needed to explain onset and recurrence of unipolar depression. Through machine learning approaches as well as SEM analysis interactions between biomarkers can be examined instead of investigating biomarkers separately [117].

### Translational psychiatry and precision psychiatry

Numerous approaches to improve psychiatric diagnostics and therapy can already be found in the scientific literature. Nevertheless, there is only slow progress concerning translation of psychiatric findings into practice, which is in literature often referred to as the “translational gap” [118]. Health care professionals often do not know what positive impact the implementation of new programs will have on their patients, with datasets that are mainly gathered in hospitals and rarely in an outpatient setting [119, 120]. Often MRI imaging and expensive biomarkers are supposedly needed to implement current findings which are usually too cost-intensive to retrieve in primary care [121]. This led us to focus on biomarkers which are easy to retrieve in an outpatient setting. Laboratory testing of Cortisol, TSH, AAT-1, IGF-1 and CRP is usually possible in an outpatient setting. IGF-1 is measured for the evaluation of hormone status and is thus also frequently part of the standard services of laboratory medical facilities. Making the panel a scalable blood-biomarker panel to investigate in an outpatient setting. Similarly, HRV measurements can be easily obtained in an outpatient setting. Commercially available long-term ECG devices can typically also measure HRV, and report stress-associated parameters derived from it. Hence, this set-up reduces translational barriers concerning later implementation [122]. Since several biologically detectable disease patterns presumably can be captured under the guise of depression, it is important to also consider the interactions of relevant factors. SEM models as well as several machine learning algorithms are suitable for this purpose, since they allow researchers testing direct as well as indirect relations and take several variables into account, making it a statistical model which could provide an alternative perspective at biomarkers and their interaction in psychiatric research [123]. With machine learning approaches also non-linear associations can be explored without the need to pre-define hypotheses, enabling a broader look into different topics.

### Development of an algorithm to detect unipolar depression

The study presented here can be used to establish an algorithm that is supposed to facilitate the diagnosis of unipolar depression in an outpatient setting. Such a tool would be particularly valuable because most studies of unipolar depression are conducted primarily in the hospital setting. Currently, only about half of depressed patients in an outpatient setting are detected, where again only a fraction receives treatment [10]. Current screening rates for unipolar depression in primary care are low, despite the high socioeconomic burden, emphasizing the dire need of fast and easy to use algorithms [124]. In a further step, validation of the model by a follow-up study would be necessary [125]. Prognosis of affected people worsens if their symptomatology goes undetected for a long time [126]. Regarding the high lifetime prevalence as well as the probability of a relapse, routine screening data indicate that a routine screening for unipolar depression is cost-effective [127]. Several barriers were identified in a qualitative study. First, primary care physicians could not adequately perform the screenings due to a lack of time, and second, there was a lack of capacity to provide patients with the ideal treatment. Third, it was also observed that, due to stigmatization, patients were only honest about their symptoms if they had established the necessary basis of trust with their family doctor [124]. Having said this, the algorithm could help primary care physicians to overcome those boundaries more easily. In 2021 Fusar-Poli et al. described the potential of preventive psychiatry to profoundly improve mental health services in our society, since currently mental health services are not focussing on the prevention of unipolar depression or other mental disorders. A “one-size fits all” approach is, according to Fusar-Poli, not effective; he stresses the need for precision psychiatry together with preventive measures in a primary care setting. Often patients at risk show rather nonspecific symptoms impeding early detection in a primary care setting [128]. Through effective stratification, precision psychiatry will significantly improve medical care for individuals [129].

### Strengths and limitations of this study

The presented study has particular value since especially in Germany, outpatient samples are rare. Even more so if they are longitudinal and prospective. As a result, the comprehensive outcome measures will provide unique information about physical and emotional health of the participants. Commonalities and differences in transition pathways and outcomes will contribute to identifying groups of patients who might benefit from differing treatment approaches or who might need more intensive care early on to improve the long-term outcome. Since a prospective period of 5 years is long and the medical examinations are only annually there might be high dropout rates, because participants might move to other places or might feel less willing to participate in our study, potentially leading to an attrition bias [130]. Since healthy participants will also be recruited by flyers, especially trained and weight conscious participants might be attracted to the study because of the usage of the bioimpedance scale, potentially leading to a sampling bias.

